**Figure 1 F1:**
[figure not shown]
Study flow diagram. Time points for patient reported and clinician reported data collection in Understanding Cauda Equina Syndrome. (QoL: Quality of Life)

Clinician-entered data will be entered directly into the database using the participant’s unique study number. Imaging will be reviewed on local *p*icture *a*rchive and *c*ommunication *s*ystems (PACS) and transferred to the study team for review. Participant questionnaires will be sent out by email using unique links for each participant. If participants do not have an email address or prefer to fill out questionnaires on paper, paper or telephone versions of the questionnaires will be used. If participants do not respond to the email invitations, they will be contacted to find out whether they wish to continue with the study and to complete the questionnaires. Where patient data is routinely entered into spinal databases, surgical and outcome data from those databases will be linked anonymously to the patient record by the clinical team using the patient’s unique identifier for that database or registry.

### Data analysis

This study aims to establish the number of patients presenting with CES in the UK over 1 year. We expect approximately 20 patients per spinal centre per year depending on the population served and a total of approximately 600–1000 patients in 1 year across the UK. The incidence of CES will be established based on the number of patients identified at each unit and the catchment population of that unit. If all units in the UK participate, incidence will be calculated based on the UK population estimates. Incidence will be calculated from all patients identified as being eligible for the study from referral screening and local coding departments, even if they do not consent for further participation.

A descriptive analysis of the clinical and demographic characteristics of presenting symptoms, signs and outcomes of patients with CES will be performed. This will be determined from both clinician-reported and patient-reported data. CES incidence and characteristics will be broken down into categories such as suspected CES, incomplete CES, with retention CES and early CES, based on the clinical data. The categorical and quantitative findings on imaging will also be described. Methods of patient presentation to specialist services will be described. Type, timings and findings of investigations in patients presenting via different routes will be compared. The investigation and management of patients with CES will be described and compared with that laid out in current care quality standards. Proportions meeting the standards will be reported. Patient outcomes will be assessed and analysed using both clinician-reported and patient-reported outcome measures at 6 months and 1 year. Patient outcomes will be stratified by demographics, presenting features, causative pathology, timing and findings of investigations, and timing and type of surgery. Patient usage of healthcare services over the year following diagnosis and management of CES, will be assessed using both patient-reported service usage and electronic records.

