## Methods and analysis

Understanding Cauda Equina Syndrome (UCES) is a prospective cohort study of patients with confirmed CES managed at specialist spinal centres in the UK. Cases will be identified by neurosurgical or orthopaedic trainees in each specialist centre through daily screening of tertiary referrals and admissions to specialist spinal services. All patients managed as CES by the treating team will be included in this study.

Data regarding timing and type of symptom onset, referral, investigation, management and outcome will be recorded anonymously on a secure database by the local trainee investigator during the patient’s hospital admission and after discharge. Patients' consent will be sought for the use of their data and they will be asked to complete patient-reported outcome measures representing their condition before surgery and up to 1 year after surgery. Imaging at presentation will also be collected. This data will be compared with care quality statements and published outcome data for CES. This is an observational study. No changes to routine patient care will occur during this study.

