### Participant selection

The study will recruit patients for 1 year. Cases will be identified from admissions to spinal units between 1 June 2018 and 31 May 2019. The last 1-year follow-up assessments will be sent to participants on 31 May 2020.

For inclusion in this study, the patient must:Be over 18 years old.Be admitted to a specialist spinal service in the UK between 1 June 2018 and 31 May 2019.Have capacity to provide informed consent for participation in this study.Have a diagnosis of clinical CES and structural compression of the cauda equina on imaging as determined by the treating clinician.Clinical CES includes any of : altered saddle sensation; bladder dysfunction; bowel dysfunction; sexual dysfunction; or bilateral sciatica. This should be associated with radiological compression of the cauda equina. The cauda equina compression can be due to any cause, including but not limited to disc, tumour or infection.

There is no upper age limit as we aim to establish the demographics of those presenting with CES.

The exclusion criteria are:Children under 18 years of age.Patients undergoing emergent decompression for unilateral motor or sensory symptoms (such as foot drop), without clinical evidence of CES.Patients referred with suspected CES where the diagnosis is not confirmed;for example, patients with clinical symptoms and signs of CES but without radiological evidence of cauda equina compression.Patients not admitted to participating spinal centres in the UK.Patients admitted to a participating spinal centre before 1 June 2018 or after 31 May 2019.Patients who are unable to provide informed consent for participation in this study.

Capture-recapture methods will be used to ensure complete case ascertainment. In December 2018, June 2019 and December 2019 all local investigators will check their case ascertainment by asking their local coding departments for all discharges coded as CES using the diagnostic code from the International Classification of Diseases, 10th Revision (ICD-10) G83.4 Cauda Equina Syndrome. Any additional patients identified through this method that meet the inclusion criteria will be invited to participate.

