### Data collection

Data relating to presentation, hospital admission, investigations and follow-up will be collected by the local trainee investigator. Data will be collected from the patient’s notes, through routine interaction with the patient as part of clinical care, and through interaction with other staff members caring for the patient. All clinical and demographic information collected for this study by the local investigators will be collected routinely. No extra assessments will be performed.

Study participants who have consented to participate will also be asked to fill out details about their patient journey, their symptoms, patient reported outcome measures and service usage. These will be collected electronically and anonymously via the electronic database and linked to the patient record. Patient reported outcome measures will include visual analogue scores for back and leg pain plus relevant sections of the Oswestry Disability Index,^22^ the neurogenic bowel dysfunction score,^23^ the short form incontinence questionnaire^24^ and the Arizona sexual experiences scale.^25^

All patients who are eligible for inclusion in the study will have basic anonymous clinical data collected as part of the screening log to establish participation rates and incidence at each centre. This will allow accurate assessment of the incidence of CES. Patients who do not wish to participate in the study will not be contacted further for the completion of patient reported outcome measures.

The timing and type of clinician reported and patient reported data that will be collected for UCES is shown in figure 1:Study flow diagram.

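### The incidence numerator is limited to eligible patients, and eligibility requires capacity to consent, so confirmed CES with lasting incapacity is left out of a count set against the whole population

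*Protocol article*

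**What the plan says.** All references are to the Protocol article.

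- **Target.** Data analysis: "This study aims to establish the number of patients presenting with CES in the UK over 1 year".
- **Numerator.** Data analysis: "Incidence will be calculated from all patients identified as being eligible for the study from referral screening and local coding departments", with the extension "even if they do not consent for further participation".
- **Eligibility.** Participant selection lists as an inclusion criterion "Have capacity to provide informed consent for participation in this study" and as an exclusion criterion "Patients who are unable to provide informed consent for participation in this study".
- **Screening log.** Data collection: "All patients who are eligible for inclusion in the study will have basic anonymous clinical data collected as part of the screening log". The section gives accurate incidence as the purpose of this log.
- **Coding check.** Participant selection adds three checks of discharges coded as CES. On the cases they find it says: "Any additional patients identified through this method that meet the inclusion criteria will be invited to participate".
- **Denominator.** Data analysis uses the catchment population of each unit, or UK population estimates if every unit takes part. Neither is restricted to people with capacity.
- **Overview.** The opening of Methods and analysis says: "All patients managed as CES by the treating team will be included in this study". No capacity condition is attached there.

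**The concern.** The plan intends an incidence that does not depend on consent. It counts people who decline, and under Patient consent it keeps basic details of people who withdraw so that incidence can still be estimated. Capacity is needed for consent and questionnaires. Counting a case in an anonymous log does not need it. Because the numerator is defined through eligibility, the capacity rule carries over into the count.

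Numerator and denominator then describe different groups: cases able to consent, over everyone in the catchment. Incidence is one of the study's main outputs, and Participant selection leaves out an upper age limit so that the demographics of presenting patients can be established. A systematic loss of one group would affect both. The loss could not be bounded afterwards if excluded cases are not recorded.

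**Working it through.** **1. The plan's own reference rate.** The Introduction gives 981 decompressions for CES in England in 2010–2011 and a population of 52 234 000.

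981 / 52 234 000 × 100 000 = 1.878, which rounds to the stated 1.9 per 100 000. The figure reproduces.

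**2. Does any rule bring in a confirmed case without capacity?**

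| Rule | Whom it covers | Adds cases who never had capacity? |
|---|---|---|
| Numerator (Data analysis) | Eligible patients | No |
| Non-consent clause (Data analysis) | Eligible patients who decline | No |
| Screening log (Data collection) | Eligible patients | Not as stated |
| Coding check (Participant selection) | Extra cases meeting the inclusion criteria | No |
| Loss of capacity during the study (Patient consent) | Participants who had already consented | No |

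No stated rule does so.

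**3. Size.** Let f be the share of confirmed cases with lasting incapacity. The article does not give f, so 1–10% is assumed. The expected total of 600–1000 (Data analysis) is taken as the true number of confirmed cases N.

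- Cases missed = N × f
- Observed rate = true rate × (1 − f), with 1.878 used as an illustrative true rate

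| f (assumed) | Missed, N = 600 | Missed, N = 1000 | 1.878 reads as |
|---|---|---|---|
| 1% | 6 | 10 | 1.86 |
| 2% | 12 | 20 | 1.84 |
| 5% | 30 | 50 | 1.78 |
| 10% | 60 | 100 | 1.69 |

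**4. Comparison with random error.** The relative 95% half-width of a Poisson count is 1.96 / √N.

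- N = 600: 1.96 / √600 = 0.080, or 8.0%
- N = 1000: 1.96 / √1000 = 0.062, or 6.2%

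The relative undercount equals f. It therefore exceeds the half-width only when f is above about 6% (N = 1000) to 8% (N = 600). The half-width shrinks as N grows; f does not.

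**The case against.** The strongest reply is that the capacity criteria concern participation, and that Data analysis separates being counted from further participation. The same section also says incidence rests on the number of patients identified at each unit, which is wider. On that reading capacity governs only the consented cohort. The reading is possible but weaker: the same paragraph then limits the numerator to eligible patients, and the non-consent clause qualifies patients who are already eligible.

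Four further points stand and limit the concern.

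- A reader might infer that patients without capacity are never written down anywhere. The article says what is logged for eligible patients. It does not say that other screened patients are left off the log, and a condensed article may omit that detail. What it does fix is that they are not in the numerator.
- A reader might infer that everyone who is delirious or critically ill is lost. The article does not fix when capacity must be present, Patient consent allows telephone consent after discharge, and the coding checks run until December 2019. Temporary incapacity may be recovered, so the clear loss is lasting incapacity.
- A reader might infer that the loss falls on older patients or on tumour and infection cases. That is plausible, but nothing in the article shows it.
- A reader might see a flat contradiction between the overview sentence in Methods and analysis and the criteria. The overview comes before the formal criteria and is better described as loose wording that they narrow.

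The size is also modest. The Introduction sets estimates below 1 per 100 000 against 1.9, and no assumed value of f would change which of these the study supports.

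**Conclusion.** The concern holds as a defect in a stated rule: the numerator is defined more narrowly than both the denominator and the stated target. Confirmed cases with lasting incapacity are not counted, and the resulting bias is downward whatever the number of cases. Its size is unknown. Under the assumed 1–10%, it is 6–100 cases in 600–1000, and for most of that range it is smaller than the random error of the count. The documents do not support calling it a large error in the national rate, or asserting a particular age or cause pattern. The case for acting is that the bias affects a main output, does not average out, and cannot be quantified later unless excluded cases are recorded.

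**What to change.** 1. Define an incidence and epidemiology population by the age, clinical, imaging, centre and date criteria, regardless of capacity or consent. Use it for incidence and for the basic descriptive data held in the log.
2. Add a field for lack of capacity to the existing anonymous screening log, and apply the same rule to cases found by the coding checks.
3. Keep capacity as a criterion for the consented follow-up cohort only.
4. Align the overview sentence in Methods and analysis with Participant selection.
5. If approval for step 2 is not obtained, state that incidence refers to adults able to consent and, where permitted, report how many were excluded for incapacity.

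The cost is a small amount of extra logging and an ethics submission, possibly an amendment. Nothing in the article shows that the existing favourable opinion covers recording data on adults without capacity. No patient contact is needed, and people who decline are already logged in the same anonymous way.

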### Patient and public involvement

The design and aims of this study were discussed with current patients being investigated for CES, and those who had previously been treated for CES. Patients trialled the questionnaires and provided feedback on the questionnaires and patient information leaflet. The length and content of the questionnaires and information leaflet were altered in response to patient feedback. All participants will receive a summary of the results of this study. Patients are not involved in recruitment to this study as this occurs during or after emergency admission to hospital with CES.

## Ethics and dissemination

### Patient consent

Once patients are identified as being eligible to participate in the study, they will be asked by a member of their clinical team whether they would be willing to receive further information about the study. For the majority of patients this will occur during their admission to the spinal unit, and the approach will be made by a member of ward medical or nursing staff. Once verbal consent is gained to give further information about the study, patients will be provided with the information leaflet for the study. Patients who indicate that they are happy to have further discussions regarding the study will be visited in hospital by a member of their clinical team to complete the written consent process. The person undertaking written consent will be adequately trained to do so, and have a good knowledge of the study protocol, aims and processes. The participant will be informed about and consent to their medical records being inspected by regulatory authorities and representatives of the sponsor. Both the participant and the person undertaking the consent will sign and date the informed consent form to confirm that consent has been obtained. The participant will receive a copy of this document and a copy will be filed in the Investigator Site File.

Decompression surgery for CES takes place as an emergency and admissions occur at all times of day and night, throughout the week and weekends. Following decompression, the length of stay in hospital wards may be as short as 1–2 days, or may be longer than a week when there are ongoing bladder or bowel problems. All patients will be given adequate time to read the information leaflet with a minimum time period of 6 hours. Some patients will be discharged prior to being identified as being eligible for the study. These patients will be contacted by telephone by a member of the clinical team and asked if they would be willing to receive information about the study by post or email. If they agree, the information leaflet and consent form will be sent to them, and they will be re-contacted to go through the consent process over the telephone at least 24 hours after receiving the information.

When participants prefer to fill out paper questionnaires or do not respond to the email link, their contact details (name, address and telephone number) will be passed to the central study team at NHS Lothian using the NHS email system with the consent of the patient. The central study team will contact the participants to find out whether they still wish to take part in the study. Those who wish to continue with the study will be sent the questionnaires by email, by post or they can be completed over the telephone with a member of the central study team depending on the preference of the participant. If participants do not wish to continue with the study, they will not be contacted further.

Participants are free to withdraw from the study at any point. If withdrawal occurs, the primary reason for withdrawal will be documented in the participant’s electronic case report form. The participant will not be contacted any further for outcome measures but their basic anonymous clinical details will be retained to allow accurate epidemiological assessment of the incidence of CES. If a patient loses capacity to consent for ongoing participation during the course of the study, the data they have already submitted or has already been submitted by their clinical team with their consent will continue to be used in the study, but they will not be contacted with further questionnaires.

### Data protection

All Investigators and study site staff involved with this study will comply with the requirements of the Data Protection Act 1998 with regard to the collection, storage, processing and disclosure of personal information and will uphold the Act’s core principles. Access to collated participant data will be restricted to individuals from the research team treating the participants, representatives of the sponsor and representatives of regulatory authorities. Computers used to collate the data will have limited-access measures via user names and passwords. Published results will not contain any personal data that could allow identification of individual participants.

All clinical details will be entered into a database hosted by Castor EDC. Castor EDC complies with all applicable laws and regulations: Good Clinical Practice (GCP), European Union Annex 11 and the European Data Protection Directive. Clinician-entered data will be entered directly into the database using the participant’s unique study number. The clinical team can only view the records of patients from their own centre. Once participants have consented for their email addresses to be stored, these will be entered into the Castor database by the local clinical team. The email address field is stored securely and is encrypted and cannot be viewed by anyone outside of the patient’s local centre.

All local investigators will store a copy of the link between the patient’s unique study number and their contact details, National Health Service (NHS) number, hospital number, Community Health Index number, unique identifiers for spinal databases or registries or other identifying details on a secure password protected NHS computer. Consent forms and paper completed questionnaires will be stored securely in a locked NHS office. No identifying information will be entered into the secure database except the email address.

All identifiable scans will be stored and transferred within the NHS PACS network. Only anonymised scans will be processed outside the NHS PACS network. Anonymised imaging data will be labelled only with the study number and stored on anonymised CDs or on encrypted hard drives.

### Data retention

All study documentation will be kept for a minimum of 5 years from the end of the study. When the minimum retention period has elapsed, study documentation will not be destroyed without permission from the sponsor. The end of the study is 18 months after the enrolment of the last participant.

### Insurance and indemnity

Sites participating in the study will be liable for clinical negligence and other negligent harm to individuals taking part in the study and covered by the duty of care owed to them by the sites concerned. The sponsor requires individual sites participating in the study to arrange for their own insurance or indemnity in respect of these liabilities. Sites which are part of the UK NHS will have the benefit of NHS Indemnity.

### Ethical review

The study will be conducted in accordance with the principles of the International Conference on Harmonisation Tripartite Guideline for GCP. All researchers are encouraged to undertake GCP training in order to understand the principles of GCP. However, this is not a mandatory requirement. GCP training status for all investigators should be indicated in their respective curriculum vitaes.

Local management approvals must be in place at each site prior to recruitment of patients to this study. The most recent version of the protocol will be available on the website of the BNTRC at www.bntrc.org.uk. This study is sponsored by NHS Lothian.

